#### Baseline

At baseline, we will assess eligibility by using the Structured Clinical Interview for Axis II Personality Disorders (SCID-II) [11]. The SCID-II provides a reliable assessment of BPD [12], has a shorter administration time than other semi-structured interviews used to assess BPD, and can be completed within 1 h. We will use data from the SCID-II to establish the severity of the participant’s personality disorder [13]. We will use the Structured Clinical Interview for Axis I Disorders (SCID-I) [14] to assess whether potential participants have bipolar affective disorder (type I and II) and to exclude those who do. Hypomanic symptoms will be assessed by using the Hypomanic Checklist [15], a relatively short screening questionnaire that can distinguish those with bipolar disorder from those with unipolar depression.

#### Primary outcome

The primary outcome is symptoms of BPD measured by using the Zanarini Rating Scale for Borderline Personality Disorder (ZAN-BPD) [16] 52 weeks after randomization. The ZAN-BPD is a widely used measure of symptoms and behavioural problems experienced by people with BPD. It includes measures of anger, impulsivity, and affective instability. The ZAN-BPD has been used in previous studies of pharmacological and psychological treatments for people with BPD [10, 17, 18]. It is reliable (intraclass correlation coefficients for inter-rater reliability of 0.96 and test-retest reliability of 0.93), has high convergent validity with structured clinical ratings of symptoms of BPD (e.g., Revised Diagnostic Interview for Borderlines), and is sensitive to change [16].

#### Secondary outcomes

Scores on the ZAN-BPD in the 52 weeks after randomization using repeated measures analysis of data collected at 12-, 26-, and 52-week follow-up.Total score on the 21-item Beck Depression Inventory [19] at 12, 24, and 52 weeks. The Beck Depression Inventory has been widely used as a self-completed questionnaire, provides a valid assessment of the severity of depressive symptoms, and can be completed in less than 10 min [20].Incidence and severity of suicidal behaviour, assessed by using the Acts of Deliberate Self-Harm Inventory [21] at 12, 24, and 52 weeks. This structured interview collects detailed information about the number and severity of episodes of self-harm and has been used successfully in other trials of treatments for people with BPD [22].Social functioning, assessed by using the Social Functioning Questionnaire at 12, 24, and 52 weeks. This questionnaire is an eight-item self-report scale that asks people about problems across a range of settings that people with personality disorder often experience [23].Health-related quality of life, assessed by using the EuroQoL-5D (European quality of Life-5 dimensions) [24] at 12, 24, and 52 weeks. The EuroQOL-5D provides a brief and reliable measure of health-related quality of life and is responsive to change in people with BPD [25].Side effects, assessed at 12, 24, and 52 weeks by using a pro forma designed to cover the possible side effects listed in the British National Formulary entry for lamotrigine [26].Use of alcohol and other drugs at 52 weeks, assessed by using the Alcohol, Smoking and Substance Involvement Screening Test (ASSIST) [27]. This short questionnaire provides a reliable and valid screening test for problem substance use [28].Use of concomitant anti-psychotic and other psychotropic medication defined as the proportion of people taking anti-psychotics, anti-depressants, benzodiazepines, and hypnotics 24 and 52 weeks after randomization.Total cost of health and social services; resource use information will be collected at 12, 24, and 52 weeks by using the Adult Service Use Schedule adapted for use in this trial on the basis of previous research involving people with personality disorders [29]. This questionnaire collects detailed data on the use of all hospital and community health and social care services.

All assessments will be conducted by researchers who have been trained to use study instruments by clinicians with expertise in the assessment of people with personality disorder.

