### Research objectives

The main objectives of the study are to find out whether adding lamotrigine to usual care for people with BPD, compared with those prescribed an inert placebo, improves mental health, social functioning, and quality of life and whether it reduces the incidence of suicidal behaviour and lowers the amount of anti-psychotic and other psychotropic medication that people are prescribed. We will also examine whether adding lamotrigine to usual care for people with BPD, compared with those prescribed an inert placebo, is associated with a higher incidence of side effects and whether adding lamotrigine provides a cost-effective use of resources.

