### Interventions

Those in the active arm of the trial will receive encapsulated generic lamotrigine titrated according to the established British National Formulary protocol (http://www.bnf.org/bnf/index.htm) but with the titration occurring at standardised 14-day intervals. The dose will be altered if participants are also taking the combined oral contraceptive pill, which affects the metabolism of lamotrigine. For those not taking the combined oral contraceptive pill, the starting dose will be 25 mg per day. Depending on the response and tolerance, it will be increased to 50 mg after 2 weeks, 100 mg after 4 weeks, and 200 mg per day after 6 weeks and thereafter. For those who are taking the combined oral contraceptive pill, the starting dose will be 25 mg per day. This will be increased to 50 mg after 2 weeks, 100 mg after 4 weeks, 200 mg after 6 weeks, 300 mg after 8 weeks, and 400 mg per day after 10 weeks.

Trial medication will be issued to patients fortnightly to cover the dose titration period, and subsequent 4-weekly packs will be issued once the maintenance dose is reached. This will ensure that non-adherence and subsequent study withdrawal are dealt with promptly and that large supplies of medication cannot be accumulated by patients who may be at risk of overdosing. Supplies will be issued by the relevant hospital pharmacy services. The lamotrigine and placebo capsules will be kept in a suitable temperature-controlled environment at each site.

Those in the placebo arm of the trial will receive capsules, identical in appearance to those containing active lamotrigine, but backfilled instead with lactose monohydrate. This will be prescribed in the same regime as that used in the active arm of the trial.

Usual care will comprise contact with primary and secondary health services, including access to psychological treatment services and inpatient admission if required. No restrictions will be imposed on the use of other treatments, except that those who remain in the trial will not be prescribed lamotrigine (aside from trial medication) or another anti-epileptic mood stabilizer (lithium, carbamazepine, or sodium valproate). Therefore, our approach will be primarily to record the use of all other medication, document details of dosage, and ensure the follow-up of all randomly assigned participants, irrespectively of the medication they subsequently receive.

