In accordance with the current revision of the Declaration of Helsinki (amended October 2000, with additional footnotes added 2002 and 2004), a participant will have the right to stop trial treatment and to withdraw from the trial at any time and for any reason, without prejudice to his or her future medical care by the physician or at the institution, and is not obliged to give his or her reasons for doing so. The investigator may withdraw a participant from trial treatment at any time in the interests of the participant’s health and well-being or for administrative reasons. A trial participant will be withdrawn from taking the trial medication if he or she experiences a rash that is clinically judged as being associated with lamotrigine. The date and reason for termination of treatment will be recorded. Trial follow-ups will continue after treatment has been withdrawn, unless the participant withdraws consent.

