### Assessments

The timing and sequence of all assessments are summarised in Table 1*.*

**Table 1 Tab1:** Study assessment schedule

Assessments	Screening	Baseline	12-week follow-up	24-week follow-up	52-week follow-up
Structured Clinical Interview for DSM-IV Axis II Personality disorders	X	-	-	-	-
Structured Clinical Interview for DSM-IV (SCID-I)^a^	X	-	-	-	-
Hypomanic Checklist	X	-	-	-	-
Alcohol, Smoking and Substance Involvement Screening Test (ASSIST)	X	-	-	-	X
Morisky scale	-	-	X	X	X
Zanarini Rating Scale for Borderline Personality Disorder (ZAN-BPD)	-	X	X	X	X
Beck Depression Inventory	-	X	X	X	X
Acts of Deliberate Self Harm	-	X	X	X	X
Social Functioning Scale	-	X	X	X	X
EuroQoL-5D	-	X	X	X	X
Side Effect Scale	-	X	X	X	X
Modified Adult Service User Schedule	-	X	X	X	X

*DSM-IV* Diagnostic and Statistical Manual of Mental Disorders (4th edition), *EuroQoL-5D* European quality of Life-5 dimensions

^a^Section on bipolar affective disorder (type I and II)

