#### Follow-up

The 12-, 24-, and 52-week assessments (Table 1) will be scheduled to coincide with the supplying of the participant’s study medication. Prior to preparing each new prescription, the psychiatrist or researcher will contact the participant to elicit details of any adverse events and to ascertain whether they wish to continue with the trial. If the participant continues to experience adverse event(s), further monitoring will be performed even when they are no longer being prescribed the study medication. Further follow-up by visit or telephone call will be arranged as required. All participants will be offered a £20 honoraria after completion of the 52-week follow-up interview.

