For our main secondary analysis, ZAN-BPD scores at 12, 24, and 52 weeks will be compared by using a mixed model for repeated outcome measures adjusted by the same stratification variables used for the primary analysis. We will investigate whether any treatment effects were sustained or emerged later by including an interaction term between treatment group and time in the model. In the absence of a time effect, the effectiveness parameter will be the average difference in mean ZAN-BPD score over the 52-week period along with 95 % confidence interval and exact *P* value.

Sensitivity analyses will be conducted for both analyses (i) to further adjust for any variable with marked imbalance at baseline, (ii) to investigate the impact of missing data by using multiple imputation, and (iii) to investigate the effect of treatment adherence.

Analysis of secondary outcomes will follow a similar approach by using appropriate mixed effects regression models (for example, logistic for binary outcomes) (that is, comparison at both 52-week follow-up and by using repeated measures analysis of follow-up data collected at 12, 26, and 52 weeks).

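### The objective is the incidence of side effects, but the stated analyses, at 52 weeks and by repeated measures over visits that all fall after titration, do not estimate it

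*Protocol article*

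**What the plan says.** The Research objectives section of the protocol article asks whether adding lamotrigine "is associated with a higher incidence of side effects" compared with placebo. The Secondary outcomes section gives the measure: "Side effects, assessed at 12, 24, and 52 weeks by using a pro forma designed to cover the possible side effects" that the British National Formulary lists for the drug. The assessment schedule (Table 1) shows the "Side Effect Scale" at baseline, 12, 24 and 52 weeks, with nothing between baseline and week 12. No recall period is stated.

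The Data management and analysis section sets one approach for all secondary outcomes, using mixed effects regression models: "comparison at both 52-week follow-up and by using repeated measures analysis of follow-up data collected at 12, 26, and 52 weeks". (It says 26 weeks where the schedule says 24; I take these to be the same visit.)

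Under Interventions, the dose without the combined oral contraceptive is "increased to 50 mg after 2 weeks, 100 mg after 4 weeks, and 200 mg per day after 6 weeks and thereafter". With the contraceptive, the last steps are "300 mg after 8 weeks, and 400 mg per day after 10 weeks". Rash has its own rule: the person "will be withdrawn from taking the trial medication if he or she experiences a rash that is clinically judged as being associated with lamotrigine". Stopping dates and reasons are recorded, and follow-up continues unless consent is withdrawn.

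Harms are also collected between the research visits. The Follow-up section states: "Prior to preparing each new prescription, the psychiatrist or researcher will contact the participant to elicit details of any adverse events". Supply is fortnightly during titration and four-weekly afterwards, and events that are still continuing are monitored after the drug is stopped. The abstract names adverse events and withdrawal of trial medication due to adverse effects as secondary outcomes. The Secondary outcomes section names neither.

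**The concern.** The question concerns new events over a period, but the stated analyses concern what is recorded at, or between, particular visits. That matters when the event can lead to stopping the drug and may then resolve. Participants who stop remain in the comparison as allocated. If their reaction is over before the reading that is analysed, they contribute no side effect to the lamotrigine arm. For reactions caused by the drug, the error favours lamotrigine on a safety question: the more early reactions lead to stopping and recovery, the less of the excess the visit-based comparison shows.

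**Working it through.** **1. Timing.** Inputs are the titration schedule under Interventions and Table 1.

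- Without the combined oral contraceptive: last step at week 6, first post-baseline reading at week 12; 12 − 6 = 6 weeks later.
- With it: last step at week 10; 12 − 10 = 2 weeks later.

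Every post-baseline reading therefore follows the last dose step.

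**2. What each stated analysis captures.** Take a reaction that begins and resolves during titration.

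| What the form asks about | 52-week comparison | Repeated measures (12, 24, 52 weeks) |
|---|---|---|
| Current symptoms | Not counted | Not counted at any visit |
| Time since the last assessment | Not counted: the reading covers weeks 24 to 52 | Counted at week 12 only, one reading of three |

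Neither row yields the proportion with an event from randomisation onwards. In the second row a titration-period excess of 15 points at week 12, with none at the later visits, averages to (15 + 0 + 0)/3 = 5 points if the three visits have equal weight.

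**3. Illustration of scale.** The article gives no side-effect rates, so the rates here are assumptions. Let p_c and p_t be the true incidence on placebo and lamotrigine, and let m be the share of the excess that the analysed reading misses because it was early and has resolved. Then

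observed p_t = p_t − m(p_t − p_c).

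Power uses the normal approximation for two proportions, n = 107 per arm (the number the article's sample size section requires before allowing for loss) and two-sided alpha 0.05:

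power = Φ[(d − 1.96·SE0)/SE1],

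where d is the observed difference, SE0 the pooled and SE1 the unpooled standard error.

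Example: p_c = 20%, p_t = 35%, m = 50%. Observed p_t = 35 − 0.5 × 15 = 27.5%, so d = 7.5 points. SE0 = √(0.2375 × 0.7625 × 2/107) = 0.0582. SE1 = √[(0.2 × 0.8 + 0.275 × 0.725)/107] = 0.0580. Power = Φ[(0.075 − 0.1140)/0.0580] = 25%.

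| Assumed true incidence | m = 0 | 25% | 50% | 75% |
|---|---|---|---|---|
| 20% v 35%: difference, points | 15 | 11.3 | 7.5 | 3.8 |
| Power | 69% | 47% | 25% | 10% |
| 10% v 20%: difference, points | 10 | 7.5 | 5 | 2.5 |
| Power | 54% | 36% | 20% | 8% |

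The table shows how the loss grows with m. It does not say what m is in this trial.

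**4. What the other records hold.** Fortnightly supply puts adverse-event contacts at about weeks 2, 4 and 6 (to about week 10 with the contraceptive), all before the week-12 reading. Early reactions should therefore be on record, and reasons for stopping are recorded too. But the side-effect outcome does not draw on these records, and the outcomes that would report them appear only in the abstract.

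**The case against.** The strongest reply is that harms are not collected only at three visits. A participant taken off the drug for a rash should appear as an adverse event and as a withdrawal for an adverse effect, both named in the abstract. That stands. A reader might infer that the trial would report no excess harm when there was one; the documents do not support this, because those two outcomes should show it. The defect lies in the side-effect comparison and in the mismatch between the two outcome lists.

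Second, the timing of a visit is not a recall period. Self-harm episodes and service use are collected at the same visits and must look back over the interval. This also stands: one cannot assert that the pro forma records only current symptoms, and with interval recall the week-12 reading loses nothing through timing alone. The 52-week comparison would still cover only weeks 24 to 52. Only a form asking back to randomisation would escape this, and the article describes none.

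Third, the analysis sentence is generic, and a condensed article may leave definitions to the full protocol or the SAP. This is partly right. But the article does state which comparisons will be made for secondary outcomes, and neither answers its own objective.

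Fourth, a reader might take the earlier 12-week lamotrigine trial, where 17 of 28 (61%) completed and so 39% did not, as a measure of the bias. It is not: the figure covers both arms and stopping for any reason.

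**Conclusion.** The point holds for the side-effect outcome. The objective is an incidence, all post-baseline readings follow titration, and neither stated analysis estimates incidence from randomisation. For the 52-week comparison this is true under both current-symptom and interval recall. For repeated measures, an early resolved reaction is missed under current-symptom recall and diluted under interval recall. That a participant who reacted and recovered would be scored as free of side effects at every visit is conditional: it requires a form that records current symptoms only, which the article does not say.

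The size of the bias cannot be derived from the article. It depends on the recall period, on how many reactions occur during titration, and on how many resolve before the analysed reading. None of these is given. The table of assumed rates shows only that the loss could matter. The sample size for the primary outcome is not affected.

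**What to change.** Settle the following in the SAP before database lock and unblinding:

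- Define the side-effect comparison as the cumulative proportion of all randomised participants with any new or worsened side effect from randomisation to 52 weeks, relative to the baseline Side Effect Scale. Combine all pro forma readings with adverse events recorded at prescription contacts and the recorded reasons for stopping.
- Add a rate per person-time under adverse-event enquiry. Contact is tied to prescriptions and may be less frequent after stopping, so a crude count could compare unequal observation if the arms stop at different rates.
- Keep prevalence at 12, 24 and 52 weeks as description.
- Add adverse events and withdrawal due to adverse effects to the secondary outcome list, so that it matches the abstract.
- State the recall period of the form in use, and leave its wording alone. The article reports 218 of the planned 252 participants recruited by the end of May 2015, so a change now would mix recall periods within the trial.

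No new data collection is needed. The cost is analysis-plan wording and the coding of free-text adverse events to the pro forma items, done while blinded.

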#### Adherence

Adherence with study medication will be assessed at 12-, 24-, and 52-week assessments by using the Morisky Scale [30]. This is a four-item questionnaire which provides a valid estimate of adherence with psychotropic medication. In addition, researchers will ask participants about their use of medication when each prescription is renewed and record any treatment breaks.

### Sample size

The sample size calculation for the study is based on our primary hypotheses that, for people with BPD who are in contact with mental health services, the addition of lamotrigine to their usual treatment will reduce symptoms of their disorder at 52-week follow-up, according to the ZAN-BPD. The ZAN-BPD has been used to examine the clinical effectiveness of a range of psychological and pharmacological treatments for people with BPD. In a trial of problem-solving therapy compared with treatment as usual, Blum and colleagues [17] found improvements in mental health and reduced use of emergency medical services among those who were randomly assigned to problem-solving therapy. This was associated with a difference of 3.6 (standard deviation (SD) = 6.9) in total ZAN-BPD score.

The ZAN-BPD rating scale was also used to examine the clinical effectiveness of lamotrigine for people with BPD in a randomized trial conducted by Reich and colleagues [10]. In this small trial (*n* = 28), a non-statistically significant difference in total score (5.6, SD = 6.75) on the ZAN-BPD was found at 12 weeks. Seventeen people (61 %) in the trial completed all 12 weeks of the study, and levels of adherence to trial medications in those who completed the study were judged to be high.

It is anticipated that levels of adherence to trial medications may be lower than in the study by Reich and colleagues, and the study has been powered on the basis of a minimal clinically significant difference in ZAN-BPD score of 3.0 (SD = 6.75). The sample size was calculated by using Stata version 13 (StataCorp LP, College Station, TX, USA).

Two hundred fourteen participants (107 receiving lamotrigine and 107 receiving placebo) would need to be randomly assigned to have 90 % power to detect a minimal clinically relevant difference of 3.0 (SD = 6.75) in total score on the ZAN-BPD at 52 weeks by using a 0.05 two-sided level of statistical significance. To take account of 15 % loss to follow-up at 52 weeks, sample size has been increased to 252.

### Assignment of interventions

After consenting to participation and completing screening assessments, patients who are found to be eligible will be randomly allocated to the intervention or comparator arm of the trial by the automated randomization service operated by Nottingham Clinical Trials Unit. Equal numbers of participants will be randomly assigned to each arm of the trial. Stratification will occur by study centre, severity of personality disorder (simple or complex personality disorder according to criteria developed by Tyrer and Johnson [13]), and extent of bipolarity (using a score of more or less than 14 on the Hypomania Checklist [15]).

### Blinding

The randomization service will generate a unique trial identification number for that participant, which will be used on the case report forms (CRFs). Blinding of investigators, researchers, clinicians, and patients will be maintained until all data entry and processing are complete and the database has been locked. All patients, carers, and study personnel will be blinded to treatment assignment. The study statistician will also be blind to trial arm allocation. Premature disclosure of allocation runs the risk of introducing bias and invalidating the trial results. Therefore, masking of treatment allocation will be maintained during the course of the trial unless the following occur: a serious adverse event arises that clinically requires disclosure, a trial drug overdose that requires disclosure occurs, or the participant becomes pregnant.

In anticipation of an emergency, investigators, clinicians, and participants will be provided with the telephone number for a 24-h emergency unblinding service at the Medical Toxicology and Information Services, which offers medical support. This system will allow a medical request for unblinding in the event of a medical emergency to be responded to 24 h a day, 7 days a week. Procedures will be put in place to verify the identity of the participant and caller, and the decision on whether to reveal the study medication allocation will be based on a set of criteria for judging clinical need. All requests for unblinding will be recorded.

After the completion of the 52-week follow-up assessment and regardless of whether they withdraw from the study early or complete the participation period in full, an email will be sent to the referring psychiatrist informing them of the participant’s trial arm allocation. Where a participant has completed the participation period in full, this will allow the prescriber time to make arrangements for the participant to continue on lamotrigine if appropriate and desired. Upon completion of their 52-week follow-up assessment, the participant will be advised to contact their psychiatrist to discuss their trial arm allocation if he or she wishes to know whether they were taking the active or placebo medication.

